#### **4.2. EXCLUSION CRITERIA**

1. Clinically important pulmonary disease other than COPD (e.g. active lung infection, clinically significant bronchiectasis, pulmonary fibrosis, cystic fibrosis, hypoventilation syndrome associated with obesity, lung cancer, alpha 1 anti-trypsin. deficiency and

---

primary ciliary dyskinesia) or another diagnosed pulmonary or systemic disease that is associated with elevated peripheral eosinophil counts (e.g. allergic bronchopulmonary aspergillosis/mycosis, Churg-Strauss syndrome, hypereosinophilic syndrome).

2. Female Any disorder, including, but not limited to, cardiovascular, gastrointestinal, hepatic, renal, neurological, musculoskeletal, infectious, endocrine, metabolic, haematological, psychiatric, or major physical impairment that is not stable in the opinion of the Investigator and could:

- Affect the safety of the subject throughout the study
- Influence the findings of the study or their interpretation
- Impede the subject's ability to complete the entire duration of study

3. Documented Unstable ischemic heart disease, arrhythmia, cardiomyopathy, heart failure, renal failure, uncontrolled hypertension as defined by the Investigator, or any other relevant cardiovascular disorder as judged by the Investigator that in Investigator's judgment may put the patient at risk or negatively affect the outcome of the study.

4. Treatment with systemic corticosteroids and/or antibiotics, and/or hospitalization for a COPD exacerbation within 4 weeks prior to (Visit 1)

5. Acute upper or lower respiratory infection requiring antibiotics or antiviral medication within 4 weeks prior to (Visit 1)

6. Pneumonia within 4 weeks prior to (Visit 1), based on the last day of antibiotic treatment or hospitalization date, whatever occurred later. The subject cannot be re-screened if this exclusion criterion is met.

7. History of anaphylaxis to Tacholiquin ®.

8. Long term oxygen therapy (LTOT) with signs and/or symptoms of cor pulmonale, right ventricular failure or evidence by echocardiogram or pulmonary artery catheterization of moderate to severe pulmonary hypertension. In order to be admitted to the trial subjects on LTOT have to be ambulatory and be able to attend clinic visits.

9. Any clinically significant abnormal findings in physical examination, vital signs, haematology, or urinalysis during Visit 1, which, in the opinion of the Investigator, may put the subject at risk because of his/her participation in the study, or may influence the results of the study, or the subject's ability to complete entire duration of the study.

10. Use of immunosuppressive medication, including rectal corticosteroids, high potency topical corticosteroids and systemic steroids within 28 days prior to (Visit 1).

### **4.3. WITHDRAWAL CRITERIA**

Reasons that a patient may discontinue participation in a clinical study are considered to constitute one of the following:

1. Occurrence of serious adverse drug reactions (at least in suspected relationship with study medication) or of other intolerable adverse events, as judged by the investigator
2. Development of any pathology, condition or surgery defined in the exclusion criteria (major protocol violation).
3. Protocol violation
4. Pregnancy
5. Subject who withdraw consent
6. Lost to follow-up
7. Administrative problems
8. Death

The reason for withdrawal must be reported on the CRF "Terminal Study Status" page and all study medication have to be returned. For withdrawn patient a full examination according to the last planned visit should be performed, whenever possible.

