### **3 STUDY DESIGN**

The study will be a monocentre, randomized, double-blind, crossover, placebo-controlled study in 24 COPD patients (including 4 Drop-out) in order to achieve 20 evaluable patients for the statistical analysis. 'Evaluable' mean eligible COPD patients having met all the inclusion and none of the exclusion criteria, having performed all scheduled clinical visits and with a "good" compliance as defined in section 7.5.

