**6.3. REPLACEMENT OF DROP-OUTS AND WITHDRAWALS**

It will be documented whether or not each patient completed the clinical study. If for any patient either study treatment were discontinued the reason will be recorded. Patients terminating the study prematurely will not be replaced. An estimation of 4 patients dropping out of the study has been considered when determining the number of patients to be recruited.

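### Section 4.3 lets a patient leave the study for an ungraded protocol violation; if that exit is used before phase B, the patient is lost to the paired ITT analyses

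*Protocol*

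**What the plan says.** Protocol 4.3 opens with "Reasons that a patient may discontinue participation in a clinical study are considered to constitute one of the following" and gives eight items. The third is "3. Protocol violation", with no grade, threshold or safety qualifier. The first item covers serious drug reactions and intolerable adverse events. The second covers exclusion conditions that develop during the study and is itself labelled a major violation. Pregnancy, withdrawn consent, loss to follow-up, administrative problems and death are listed separately.

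After withdrawal, "all study medication have to be returned", and "For withdrawn patient a full examination according to the last planned visit should be performed, whenever possible".

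Section 6.3 adds two records: "It will be documented whether or not each patient completed the clinical study" and "If for any patient either study treatment were discontinued the reason will be recorded". Leavers are not replaced, and "An estimation of 4 patients dropping out of the study has been considered". Neither section says whether a violator continues into phase B.

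On the analysis side, sections 2.2, 7.1.1 and 9.4 make the primary endpoint the week-3 sputum weight on tyloxapol minus that on saline. It is tested by t-test in the Per Protocol population and, in 7.1.1 and 9.4, repeated in ITT. Section 9.4 applies the same method, in ITT, to the secondary endpoints and to the acute sputum change on day 1. Section 3 restricts evaluable patients to those who are eligible, comply well and are described as "having performed all scheduled clinical visits". Section 9.2 has problem cases discussed, and the populations defined, at a blinded review before decoding.

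**The concern.** The ITT repeat is the check on a primary result that comes from the Per Protocol set, and ITT is the main set for the secondary endpoints. Both lose that purpose to some degree if patients can be taken out after randomisation for reasons that ITT is meant to tolerate, such as a missed visit window, poor compliance or a disallowed drug. Safety and new exclusion conditions already have their own items, so the third item mainly adds deviations of this lesser kind.

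The crossover sharpens the problem. In a parallel-group trial an early leaver may still supply a value for the assigned arm. Here the second treatment is given only in phase B (5.3), so a patient who leaves in phase A or washout has no value on it and no difference can be formed. This is a rule of conduct: neither an analysis plan nor the blind review can recover an observation that was never made.

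The exit is also not needed to keep violators out of the Per Protocol analysis. Sections 3 and 9.2 already do that, later and blinded.

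**Working it through.** **1. The plan's own figure.** Inputs from 9.3 and 9.5: difference 1.2 g, s = 1.7 g taken as the SD of the within-patient difference, two-sided alpha 0.05, 20 patients, 80% power. For a paired t-test the noncentrality is (1.2/1.7) × √n with n − 1 degrees of freedom.

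| Complete pairs | Power |
|---|---|
| 24 | 91.2% |
| 20 | 84.9% |
| 19 | 82.9% |
| 18 | 80.6% |
| 17 | 78.0% |

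The smallest n for 80% is 18, so the stated 20 is slightly conservative. Power drops below 80% only when fewer than 18 pairs remain. That means more than 24 − 18 = 6 losses from the 24 of section 3, or more than 20 − 18 = 2 from the 20 allocated in the synopsis.

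**2. What a violator who leaves before phase B can contribute.**

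- *Primary difference, ITT repeat:* at most one week-3 value, so no pair.
- *Secondary endpoints under the paired method of 9.4, including the day-1 sputum change:* no phase B value, so no pair.
- *Lung function:* the spirometry part of 6.2.2 also specifies a by-visit analysis of covariance. That model can use phase A data, so lung function is not lost altogether.
- *Per Protocol:* leaving breaks the all-visits condition of section 3. A minor violator whom the blind review would have kept is therefore lost here as well.

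A patient who leaves during phase B is in a different position: the exit examination may yield a value on the second treatment, although an early one. The certain loss is confined to exits before phase B.

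**3. How far the ITT estimate could move (illustration).** The protocol does not say how many patients would leave under the third item or what their true difference would be. Assume m completers at 1.2 g and k violators with true difference d between 0 and 2.4 g. If the violators were kept:

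ITT mean = (m × 1.2 + k × d) / (m + k)

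| Scenario | d = 0 | d = 1.2 | d = 2.4 |
|---|---|---|---|
| m = 20, k = 1 | 24/21 = 1.14 g | 1.20 g | 26.4/21 = 1.26 g |
| m = 20, k = 4 | 24/24 = 1.00 g | 1.20 g | 33.6/24 = 1.40 g |
| m = 18, k = 1 | 21.6/19 = 1.14 g | 1.20 g | 24/19 = 1.26 g |
| m = 18, k = 2 | 21.6/20 = 1.08 g | 1.20 g | 26.4/20 = 1.32 g |

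The rows with m = 20 follow sections 3 and 6.3 (24 enrolled, 4 drop-outs). Those with m = 18 follow the synopsis (20 allocated, 18 analysed). The rows with k = 4 and k = 2 are upper bounds, since they put every planned loss under this one item.

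**4. Precision.** The 95% CI half-width is t(0.975, n − 1) × 1.7/√n: 0.80 g at 20 pairs, 0.77 g at 21 and 0.72 g at 24. One patient shifts the mean by at most 0.06 g, which is small against that width.

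**The case against.** The strongest reply is that 4.3 is largely a catalogue of reasons for the CRF status page. Death and loss to follow-up are in it, and nobody applies those as rules. Where the protocol wants removal it says so, as after a code break (5.5.3). The visit schedule and the crossover apply to every randomised patient, 6.3 separates completing the study from stopping a treatment, and 9.2 presupposes that data on problem cases exist. On that view staying in is already the default. This stands in part: a reader might infer that violators must be removed, and the text does not say so. But the section is headed as withdrawal criteria and an ungraded violation is one of them, so a site may use it at its discretion.

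A second reply is that any exit before phase B, for any of the eight reasons, costs a pair, and that four drop-outs are allowed for. That is true, but most of the other reasons cannot be avoided and this one can.

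A third is that the size rests wholly on assumed inputs. That is also true, and no bias is demonstrated.

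A reader might also infer that everyone who stops treatment should attend all remaining visits. The documents do not support that as a remedy. Sputum is obtained after nebulising study medication (7.3.1), so those visits would recover no sputum weight, and questionnaires or spirometry off treatment add little to a comparison of tyloxapol with saline.

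**Conclusion.** The point holds in a limited, conditional form. Section 4.3 permits an avoidable exit. If it is used before phase B, the patient drops out of the paired ITT repeat and of the secondary analyses that use the same paired method. A minor violator may drop out of the Per Protocol set too. The number affected may be none, and the direction of any bias is unknown. Under the stated assumptions one such patient moves the ITT mean by up to 0.06 g. The extreme case of all four planned drop-outs moves it by up to 0.20 g.

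Two stronger readings should be resisted. A reader might infer that the trial becomes underpowered. That is not shown: the four planned losses leave 20 pairs and 84.9% power, and the synopsis count of 18 leaves 80.6%. A reader might also infer that all secondary information on a leaver is lost, but the by-visit lung-function model can still use phase A data.

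The change is worth making because it is cheap and takes a discretionary removal after randomisation out of a trial of 20 to 24 patients.

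**What to change.** In 4.3, delete the third item as a reason for ending participation. In 4.3 and 6.3, add:

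*Patients with a protocol violation who can safely continue stay on treatment and in the visit schedule through both phases, and their week-3 sputum is collected in both. Exclusion from the Per Protocol set is decided only at the blind review (9.2).*

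Keep withdrawal for safety, for newly developed exclusion conditions (second item), for pregnancy, for withdrawn consent and after a code break as written.

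The cost is a protocol amendment, which needs authority and ethics committee approval if it is classed as substantial under 14.1, and somewhat noisier ITT data. The visits are already in the schedule. How Per Protocol membership is decided does not change, except that minor violators now remain available for it.

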## **5 STUDY MEDICATION**

### **5.1. INVESTIGATIONAL DRUG**

Tacholiquin ® contains:

1% (0.1%) tyloxapol

5% glycerine

2% sodium hydrogen carbonate in a sterile aqueous solution.

Tacholiquin ® will be provided as 1% solution and inhaled via nebulizer three times daily. The preparation is available as 5 ml syringe stable for 4 weeks. Matching syringes with 5 ml 0.9% Saline will be used as placebo.

## **5.2. COMPARATOR DRUG**

Matched syringes with 5 ml 0.9% Saline will be used as comparator drug.

## **5.3. DOSAGE AND TREATMENT SCHEDULE**

The dosage regimen will be three inhalations with 5 ml solution via nebulizer per day of study treatment during 21 consecutive days. Patients will be randomized either starting with Tacholiquin ® or Saline 0.9% in treatment phase A. After treatment phase A patients will receive the alternative drug in treatment phase B.

## **5.4. SUPPLY, LABELLING AND PACKAGING ARRANGEMENTS**

All study medication will be supplied to the principal investigator by benepharma via the Central Apotheke Steinbach. The central Apotheke will deliver to the study site syringes with study treatment.

For each patient syringes with Tylaxopolor placebo will be provided for the double-blind treatment period (including 6 reserve syringes). The study medication is presented in box wallets, each containing 3X 21 syringes (for 21 days of treatment).

The patients will have to bring back their study medication package (including reserve medication) for compliance check at Visit 3 and 6.

## **5.5. METHODS OF BIAS REDUCTION**

### **5.5.1. RANDOMISATION**

Randomisation will be performed by [name] using a validated system (RandList 2.0) that automates the random assignment of treatment groups to randomisation numbers.

Treatments are randomly allocated to patients, according to the random permuted block scheme. The randomisation number will have 2 digits, starting at 01.

In accordance with the ICH Biostatistics Guideline, the block size is intentionally not given in the study protocol. The generation of the random code list including the production of sealed envelopes is performed in a validated environment.

### 5.5.2. **BLINDING**

The study is conducted as a double-blind study.

For the treatment period, the syringes with 5 ml will not differ in appearance (concerning form, weight, color, texture of content, etc.), to ensure patient and investigator blinding.

The investigators and personnel involved in study will remain blinded throughout all periods of the study, except in the case of an emergency. Study drug codes will not be available to the above personnel until completion of the clinical trial report.

### 5.5.3. **EMERGENCY CODE**

The Investigator will be provided with a sealed envelope containing the code for each patient's randomisation number. The code can only be broken under serious adverse event circumstances. If a code-break occurs, the investigator will record the reason for the code-break, the date of opening and will sign the envelope in the appropriate place, withdrawing the patient from the study. The investigator will communicate the event of breaking the code to the Sponsor.

## 5.6. **TREATMENT ASSIGNMENT**

At Visit 1 (Day 0) eligible patients will be assigned a randomization number in consecutive, ascending order.

In order to ensure random allocation, each new consecutive patient randomized is to be given the box bearing the lowest available randomisation number.

The investigator must maintain an accurate record of the shipment and dispensing of study drug in a drug accountability log. An accurate record of the date and amount of study drug dispensed to each patient and returned must be available for inspection at any time.

The investigator will be asked to return all unused medication at the end of the study.

Volunteers are required to be dosed so that the time window between visits is within 7 days of the scheduled administration dates.

## 5.7. **STORAGE CONDITIONS**

Syringes either with Tylaxopolor saline 0.9% have to be stored at room temperature (not above 25°).

Drug supplies must be kept in an appropriate, secure area (e.g. locked cabinet) and stored according to the conditions specified on the drug labels.

## 5.8. CONCOMITANT MEDICATIONS

All concomitant medication must be recorded in the CRF on the concomitant medication pages at each visit. Patient diary will also be checked at each visit to verify if patient has an AE or has taken concomitant medications.

### 5.8.1. AUTHORIZED MEDICATIONS INCLUDING RESCUE MEDICATION

Use of  $\beta$ -2 agonists (salbutamol 100  $\mu$ g 2 puffs) is allowed for the treatment of symptoms during the study. Each nebulization of salbutamol should be recorded on the patient's diary and will be included in the analysis of medication use.

## 6 STUDY PROCEDURES AND ASSESSMENTS

### 6.1. STUDY PROCEDURE

The study design is shown in Fig: 1.

[figure not shown]

#### 6.1.1. RECRUITMENT PROCEDURE

At Visit 1 before any assessment necessary for the study, the COPD patient will be informed by the physician according to the “Patient information” sheet. The patient will then give a written consent by signing the Patient Consent. As soon as the specific inclusion and exclusion criteria at Visit 1 have been checked, eligible patients will be assigned a randomization number in ascending order. They will then start double-blind trial treatment.

Additional visits can be scheduled and performed according to the investigators judgment of how to best manage the patient. At these visits in addition to recording any SAEs, AEs and concomitant medication use, a physical examination, vital sign assessment and lung function tests are to be performed.

Any unscheduled visits are to be recorded in the other clinical visits CRFs.

#### 6.1.2. **DEMOGRAPHIC DATA, BASELINE DATA**

Age, sex, ethnic origin, height, weight, smoking status, general medical history, past and concomitant medication, clinical status, allergic history, lung function at the initial visit are to be reported to check the homogeneity of the sample.

### 6.2. **PROCEDURE BY VISIT**

#### 6.2.1. **METHODS AND MEASUREMENTS**

##### **Visit procedures at screening visit and before treatment phase A (Visit 1)**

- Patient information/Informed consent
- Date of visit
- Demographic data,
- Medical history and concomitant diseases
- Physical examination / Vital signs
- Concomitant medications
- Bodyplethysmography
- Bronchodilator response to Salbutamol
- Completing Questionnaires (CAT, BDI, St George)
- Inclusion/exclusion criteria

- Randomisation and drug dispensation
- Laboratory examination (including Urinalysis)
- Inhalation of blinded medication by nebuliser
- Sputum collection
- Recording side effects
- Recording “ease of expectoration”.
- Lung function monitoring up to one hour after sputum collection
- Lung clearance index one hour after inhalation
- Dairy explanation
- Appointment for the next visit

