| OUTCOME(S)                           | The primary outcome variable is sputum weight after treatment as difference between that after Tylaxopol and after saline. Key secondary endpoint(s) are: symptom scores (CAT, BDI and TDI), ease of sputum production by analog scale, changes in lung function parameter (FVC, FEV1, MEF25, RV, RV/TLC), LCI, sputum parameters and biomarker profiles (IL-1, IL-6, IL-8), in sputum and response to Tylaxopol vs. saline. Assessment of safety: Safety will be ensured by monitoring of symptom scores and rescue medication, lung function FEV1 and adverse events. |
| DURATION OF TREATMENT AND FOLLOW-UP  | Duration of treatment per treatment arms (3 weeks): Each patient will be treated in a cross-over double-blinded randomized design either with Tylaxopol and or saline. During each treatment arm is a one week washout phase.                                                                                                                                                                                                                                                                                                                                                  |
| STUDY TYPE                           | This study is a monocenter double-blind, placebo-controlled (DBPC) crossover randomised trial.                                                                                                                                                                                                                                                                                                                                                                                                                                                                                        |

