| Inclusion/ Exclusion                          | X                                  |                   |                   |                            |                   |                    |
| Physical Examination Vital Signs              | X                                  | X                 | X                 | X                          | X                 | X                  |
| Lung function (Bodyplethys.)                  | X                                  | X                 | X                 | X                          | X                 | X                  |
| Post Reversibility Lung function              | X                                  | X                 | X                 | X                          | X                 | X                  |
| Urine Pregnancy testing           | X                                  | X                 | X                 | X                          | X                 | X                  |
| Laboratory examinations           | X                                  |                   |                   |                            |                   |                    |
| COPD Assessment Test (CAT) handover           | X                                  | X                 | X                 | X                          | X                 | X                  |
| Collection and Review of BDI / TDI St George  | X                                  |                   | X                 |                            | X                 | X                  |

---

|                                            |   |   |   |   |   |   |
|--------------------------------------------|---|---|---|---|---|---|
| Inhalation of medication                   | X | X | X | X | X | X |
| Lung function after Sputum collection      | X | X | X | X | X | X |
| Monitoring Ease of expectoration           | X | x | x | x | x | x |
| Nebulizer and Drug dispensation            | X |   |   | X |   |   |
| Collection of trial drug/ Compliance check | x | x | X | x | x | X |
| Recording of Adverse Events                |   | X | X | X | X | X |
| Appointment for the next visit             | X | X | X | X | X |   |

1) If applicabel

2) Laboratory examinations : Hematology Makrophagen Activation test

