### **2.3. SECONDARY AND EXPLORATIVE ENDPOINTS**

Secondary endpoints:

The analysis of symptom scores ((CAT, BDI,TDI and St George's respiratory Quality of Life Questionnaire), ease of sputum production by analog scale, lung function parameter (FVC, FEV1, MEF25, RV, RV/TLC), LCI will use the same methodology as that for the primary endpoint, using the ITT population. The analysis will include Day 1 and week 3 data. In addition acute changes of sputum weight on Day 1 at each treatment arm will be analyzed as described for the primary parameter.

Explorative endpoints:

Biomarker profiles (sputum cells, IL-1, IL-6, IL-8), in sputum will be analysed using an analysis of covariance (ANCOVA) model with covariates of baseline, smoking status and treatment. Estimated treatment differences along with corresponding 95 % CIs will be presented for the treatment comparison.

In addition anti-inflammatory activity of tyloxapol will be analyzed in vitro by the macrophage activation test.

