**Visit procedures after washout (+ 7-14 days) before treatment phase B at visit 4**

- Date of visit
- Physical examination / Vital signs
- Concomitant medications
- Bodyplethysmography
- Bronchodilator response to Salbutamol
- Completing Questionnaires (CAT, BDI and St. George)
- Drug dispensation
- Inhalation of blinded medication by nebuliser
- Sputum collection
- Recording side effects
- Recording “ease of expectoration”.
- Lung function monitoring up to one hour after sputum collection
- Appointment for the next visit

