**Visit procedures at visit 6 end of treatment phase B (21 ± 4 days after Visit 4)**

- Date of visit
- Physical examination / Vital signs
- Concomitant medications
- Bodyplethysmography
- Bronchodilator response to Salbutamol
- Lung clearance index
- Completing Questionnaires (CAT, TDI and St. George)
- Drug dispensation
- Inhalation of blinded medication by nebuliser
- Sputum collection
- Recording side effects
- Recording “ease of expectoration”.
- Lung function monitoring up to one hour after sputum collection

Additional visits can be scheduled and performed according to the investigators judgment of how to best manage the patient. At these visits in addition to recording any SAEs, AEs and concomitant medication use, a physical examination, vital sign assessment and lung function tests will be performed.

Any unscheduled visits, follow-up visits and adverse events, are to be recorded in the other clinical visits CRFs.

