### **Quality of life**

Quality of life measures were made using the St George's respiratory Quality of Life Questionnaire. Self-completed questionnaires were performed before and after each treatment phase. A clinically relevant change was considered to be 4 for total score. End-points included the global score change during active and placebo phases, as well as scores for the sub-scales of symptoms, activity and impact.

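### LCI is scheduled only at Visits 1 and 6, leaving no within-patient pair for its planned Day 1 and week-3 comparisons; the flow chart also contradicts section 6.2.1 on the Phase B BDI and St George baseline

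*Protocol*

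**What the plan says.** **LCI as an endpoint.** The synopsis lists "LCI, sputum parameters and biomarker profiles" among the key secondary outcomes, tyloxapol against saline. Section 2.3 states: "lung function parameter (FVC, FEV1, MEF25, RV, RV/TLC), LCI will use the same methodology as that for the primary endpoint", in the ITT population, using data from Day 1 and week 3. The primary method (section 2.2) is the value after 3 weeks of tyloxapol minus the value after 3 weeks of saline, with a 95% CI and a t-test. LCI is not named in the secondary analysis lists of the synopsis (Statistical Analysis), section 7.1.2 or section 9.4.

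**LCI in the schedule.** Section 6.2.1 has "Lung clearance index one hour after inhalation" at Visit 1 and "Lung clearance index" at Visit 6, the latter without a time relative to inhalation. The lists for Visits 2 to 5 do not contain it. The flow chart has no LCI row, and the lung function variables recorded at every visit (section 6.2.2, Pulmonary Function) do not include it.

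**Questionnaires.** The flow chart row "Collection and Review of BDI / TDI St George" is marked at Visits 1, 3, 5 and 6. Section 6.2.1 has "Completing Questionnaires (CAT, BDI and St. George" at Visit 4, before Phase B, and only CAT at Visit 5. The quality-of-life text says: "Self-completed questionnaires were performed before and after each treatment phase".

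**The concern.** The paired method needs, for each patient, a tyloxapol value and a saline value from the same time point. With LCI at Visits 1 and 6 only, each patient has a first-dose value on one treatment and a 3-week value on the other. A difference between those two mixes treatment with period and with duration of treatment. A measurement that was never taken cannot be recovered by a later analysis plan, so the visit schedule has to be right in the protocol.

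The questionnaire conflict raises a related risk. A site that works from the flow chart would collect BDI and St George 7±2 days into Phase B instead of before it. The Phase B TDI and the Phase B St George change would then have no pre-treatment reference.

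**Working it through.** The protocol gives no figure for LCI precision, so there is none to reproduce. The check is a cross-tabulation, followed by the variance of what can still be estimated.

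**1. Pairs available**

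| Time point | Visits needed | LCI scheduled at | Complete pairs per patient |
|---|---|---|---|
| Day 1 | 1 and 4 | 1 only | 0 |
| Week 3 | 3 and 6 | 6 only | 0 |

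This needs no assumption.

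**2. What V6-V1 contains.** Let T1 and S1 be the Day 1 means on tyloxapol and saline, T3 and S3 the week-3 means, and d the common shift from Visit 1 to Visit 6. Assume no carryover.

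- Tyloxapol first: V6-V1 = d + S3 - T1
- Saline first: V6-V1 = d + T3 - S1

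Within one sequence, treatment cannot be separated from d or from first dose versus 3 weeks. If active-minus-saline differences are pooled in a one-sample t-test, d enters with opposite sign in the two sequences. It then cancels from the mean only when the sequences are of equal size, and it inflates the standard deviation even then.

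Subtracting the sequence means (saline first minus tyloxapol first) removes d:

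(T3 - S1) - (S3 - T1) = (T1 - S1) + (T3 - S3)

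Half of this is the average of the Day 1 and week-3 effects. It separates neither.

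**3. Precision.** Inputs: 20 patients (section 9.3), taken as 10 per sequence; common variance s²; correlation rho between any two LCI values of a patient. Section 9.3 gives rho = 0.75 for sputum weight. No value is given for LCI, so rho is an assumption here and a range is shown.

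- Planned paired week-3 comparison: 2s²(1-rho)/20
- Between-sequence contrast of V6-V1, halved: (1/4) × 2 × 2s²(1-rho)/10 = s²(1-rho)/10, the same as the paired comparison
- Between-patient comparison at Visit 6: 2s²/10 = 0.20s²
- Ratio of Visit 6 comparison to paired comparison: 0.20/[(1-rho)/10] = 2/(1-rho)

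| rho (assumed) | Paired | Halved sequence contrast | Visit 6, 10 v 10 | Variance ratio | CI width ratio |
|---|---|---|---|---|---|
| 0.5 | 0.050s² | 0.050s² | 0.20s² | 4 | 2.0 |
| 0.75 | 0.025s² | 0.025s² | 0.20s² | 8 | 2.8 |

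**4. Questionnaires, side by side**

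| Source | BDI/TDI/St George visits |
|---|---|
| Flow chart | 1, 3, 5, 6 |
| Section 6.2.1 | 1, 3, 4, 6 |
| Quality-of-life text (St George, before and after each phase) | 1, 3, 4, 6 |

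The only mismatch is Visit 4 against Visit 5. Visits 3 and 6 appear in every source.

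**The case against.** A reader might infer that LCI cannot be compared between treatments at all, or that the schedule forces an eightfold loss of precision. The documents support neither. Sequence is randomised in permuted blocks (section 5.5.1), so the between-sequence contrast of V6-V1 is a valid comparison if there is no carryover, and its variance equals that of the paired design. A randomised between-patient comparison of first-dose values at Visit 1 is also possible. The factor of 8 applies only to isolating the week-3 effect, and only if the sputum-weight correlation also holds for LCI. This part of the objection stands. It does not rescue the plan, because section 2.3 calls for within-patient comparisons at Day 1 and week 3 and neither can be made.

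It can also be said that LCI may not be an analysed endpoint, since three of the analysis lists omit it. That is a fair question, but the synopsis outcomes and section 2.3 both name it. The conflict is one more thing to reconcile, not a reason to leave the schedule alone.

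On the questionnaires, the Visit 4 and Visit 5 procedures and the quality-of-life text agree with one another, and only the flow chart differs. A reader might infer that every patient will lack a Phase B baseline, or that the St George endpoint is lost. The first follows only if the site works from the flow chart. The second does not follow, because the end-of-phase St George comparison uses Visits 3 and 6, which all sources include.

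**Conclusion.** The point holds for the analysis as planned. No patient has a same-time-point tyloxapol/saline pair of LCI values, at Day 1 or at week 3; this rests on the visit lists alone. The computable between-sequence contrast answers a different question, the average of the two effects, and assumes no carryover. For the week-3 effect alone, the variance is 4 to 8 times that of the paired comparison for rho from 0.5 to 0.75, assuming 10 patients per sequence, equal variances and an LCI correlation that the protocol does not give.

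The flow chart conflict exposes the Phase B TDI, the Phase B St George change and the Phase B Day 1 values of BDI and St George, and nothing else. The primary endpoint and its power are untouched. Both discrepancies should be corrected, as matters of secondary endpoints.

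**What to change.** 1. In section 6.2.1, move the Visit 1 LCI to Visit 3. State one timing relative to inhalation for Visits 3 and 6, and add an LCI row to the flow chart. The week-3 comparison is then paired, with two LCI tests per patient as now.
2. In section 2.3, remove Day 1 from the LCI analysis. This is the real cost: a planned time point is given up, and with it the first-dose LCI value. If the sponsor wants both time points, Visit 1 must stay and LCI must be added at Visits 3 and 4, making four tests per patient instead of two.
3. Make LCI's status the same in the synopsis (outcomes and statistical analysis) and in sections 2.3, 7.1.2 and 9.4.
4. In the flow chart, move the BDI/TDI/St George mark from Visit 5 to Visit 4, to agree with section 6.2.1 and the quality-of-life text. The number of questionnaires does not change.

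Under the first option, all of this is protocol wording with no added assessments.
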